### 5.2 PROCEDURES FOR ASSESSING EFFICACY

#### 5.2.1 PSA MEASUREMENTS

PSA will be tested regularly at each follow-up visit and more often if clinically indicated. The assay used must have a sensitivity of 0.1ng/ml or lower.

#### 5.2.2 EFFICACY PARAMETERS

The primary outcome measure is for RADICALS-RT is freedom from distant metastasis. This will be defined as any distant metastasis or death from prostate cancer. Bone scans are not mandated at set times but should be performed as clinically indicated. The primary outcome measure for RADICALS-HD is metastasis free survival, defined as any distant metastasis or death from any cause.

All men should be followed-up for the duration of the trial. With regards to ascertaining causes of death, particular attention will be paid to men who are reported as having died from prostate cancer without previously reporting progression or recurrence, and men who are reported as having died from non-prostate cancer causes after developing hormone refractory disease. There will be a review of causes of death performed independent from allocated trial arm.

### 5.3 PROCEDURES FOR ASSESSING SAFETY

There are no tests in addition to standard practice to assess patient safety. Patients will be seen every 4 months for 2 years, every 6 months from 2 to 5 years, then annually thereafter. Secondary malignancies, toxicities and SAEs will be recorded on CRFs and/or SAE forms which will be monitored by the Independent Data Monitoring Committee (IDMC).

### 5.4 OTHER ASSESSMENTS

#### 5.4.1 PATIENT REPORTED OUTCOMES

Quality of life will be assessed using self-administered questionnaires in the subgroup of patients entered in RADICALS-RT. These questionnaires have approximately 50 questions and are collected pre-randomisation and at 1, 5 and 10 years after randomisation. Further details are given in [Section 13.1](#).

#### 5.4.2 HEALTH ECONOMICS

Data for the health economics substudy will be collected on both CRFs and patient administered questionnaires (EQ-5D). The EQ-5D questionnaire will be completed by the patients together with the patient reported outcome forms at baseline and at 1, 5 and 10 years after randomisation. Further details are given in [Section 13.2](#).

### 5.5 EARLY STOPPING OF FOLLOW-UP

If a patient chooses to discontinue their trial treatment, they should still be followed up providing they are willing; if they do not wish to remain on trial follow-up, however, their decision must be respected and the patient will be withdrawn from the trial completely. The CTU should be informed of this in writing using the appropriate documentation. Patients withdrawing from follow up have a negative impact on a trial's data.

If the medical data collected during the patient's participation in the trial are kept for research and analysis purposes, they can be anonymised if necessary. Consent for future use of stored samples already collected can be refused when leaving the trial early (but this should be discouraged and should follow a discussion).

Patients may change their minds about stopping trial follow-up at any time and re-consent to participation in the trial.

Patients who stop trial follow-up early will not be replaced.

Patients will be followed up in the long-term through usual mechanisms, which may include flagging through national registries.

### 5.6 LOSS TO FOLLOW-UP

Every effort should be made to follow-up all patients who have been randomised. Patients should, if possible, remain under the care of an oncologist or urologist for the duration of the trial. If care of a patient is returned to the primary lead physician, it is the responsibility of the trial investigator who obtained the patient's consent to participate in the trial to ensure that the data collection forms are completed. For participants who stop follow up early, data collected up to the time of withdrawal

from follow up will be kept and included in the analysis unless the participant explicitly withdraws consent for this.

If follow-up visits are no longer possible according to the trial schedule, patients can be followed up by telephone or using information from other healthcare services, e.g. GP practice. These follow-ups should adhere to the timelines specified in the patient's schedule. If information reported on the follow-up CRF is not from a follow-up visit to a RADICALS investigator site please indicate this by completing question 1a on the Follow Up CRF.

Where it applies, the consent of patients should be obtained for their names to be flagged for survival information through national registries, for example NHS Information Centre/Office of National Statistics (ONS) in England/Wales and General Register Office in Scotland, Hospital Episode Statistics (HES). If the clinician moves, appropriate arrangements should be made to arrange for trial follow-up to continue at the centre.

## **5.7 PATIENT TRANSFERS**

For patients moving from the area, every effort should be made for the patient to be followed-up at another participating trial centre and for this trial centre to take over responsibility for the patient. To document the transfer process the main contact person at both the current and receiving hospitals should complete and sign the Patient Transfer Confirmation form. A fully completed form must be returned to the CTU prior to the patient transfer and ideally any data queries for the patient should be completed prior to transfer.

On receipt of the completed transfer form a member of the RADICALS team will confirm the database has been updated and request confirmation of the name of the patient's new Clinician. Photocopies of the following documents may then be sent to the new hospital to complete the transfer and copies must be also retained at the original site for monitoring purposes:

- Consent form
- Completed CRFs
- Any documentation relating to the patient's participation in RADICALS (patient names must be removed from any documentation).

### **5.7.1 MORTALITY DATA FROM ELECTRONIC HEALTH RECORDS**

Death registration data for England and Wales became available to the trial in January 2018, to be updated quarterly thereafter. These will be provided through ONS or an appropriate alternative. This enables regular checking for completeness of the trial database, with specific data chases to sites in the event of unreported deaths becoming known. The data also enables more precise survival estimation, since patients without recent trial follow-up may be assumed to be alive approximately one month before the data extract if death has not been registered. Death registration also enables checking for unreported distant metastases, in the event of a prostate cancer death being registered with ONS but no distant metastases previously recorded in the trial database. Data from other national registers may be used in the future if it becomes available to the trial team.

## **5.8 END OF TRIAL**

All patients will be actively followed according to the trial schedule until end of funding unless the TMG considers appropriate to transition before then to a long-term follow-up stage. During the long-term follow-up stage participants will not be required to make any trial specific visits to the clinic but will be followed-up via retrospective data collection from the sites and national registries for which

consent has been requested as part of the original consent process. During this follow-up period participants will have completed the interventional phase of the study and will not be on any trial mandated regimen so real time SUSAR and SAE reporting will cease but investigators will be asked to report events via national reporting systems such as the MHRA Yellow card system in the UK.

## 6 STATISTICAL CONSIDERATIONS

### 6.1 METHOD OF RANDOMISATION

Randomisation will be performed centrally at the MRC Clinical Trials Unit at UCL using a computer-implemented algorithm. The method of randomisation will be minimisation over a number of clinically important stratification factors with an allocation probability of 80%. Each comparison will have an independent randomisation programme.

### 6.2 OUTCOME MEASURES

RADICALS considers a number of primary and secondary outcome measures; all outcome measures are relevant to both trial randomisations unless otherwise stated. All outcome measures will be timed from the relevant randomisation.

#### 6.2.1 PRIMARY OUTCOME MEASURE - RADICALS-RT

RADICALS-RT was originally designed to detect an absolute improvement of 5% in disease-specific survival at 10-years from 90% to 95% with 80% power. Since the trial was designed in 2006, further information on disease-specific survival in similar patient cohorts has become available from prospective RCTs, including EORTC 22911 (8) and SWOG 8794 (10). These provide useful estimates as they are both clinical trials and recruited partly during the PSA era; such information was not previously available. The results of these trials show that death from causes other than prostate cancer is a major competing risk, with around only one in four deaths being attributed to prostate cancer and a 10-year disease-specific-survival (DSS) of around 94%; this patient cohort is performing much better than had been anticipated originally. With further treatments (e.g. docetaxel) being available and standard of care at the time of relapse and the development of castrate-refractory disease, the time from the development of distant metastasis until death from prostate cancer has lengthened. An absolute improvement of 5% is not a reasonable assumption if these estimates hold true.

However, the role of adjuvant RT remains controversial and a clinical trial is required to resolve this issue. RADICALS-RT will do this. Therefore, focus has turned towards distant metastases, which is an earlier but clinically important and objective outcome measure. The primary outcome measure for RADICALS-RT is now **freedom-from-distant-metastasis**.

Disease-specific survival, therefore, becomes an important secondary outcome measure. At the main analysis of distant metastases, the trial would expect around 41 deaths from prostate cancer and would have 59% power to detect a halving of the risk of prostate cancer death from 6% at 10-years to 3%, ie DSS improves from 94% to 97%. With further follow-up, RADICALS-RT could attain 80% power for DSS after additional 6 years of follow-up (total duration of the trial would be 18.5 years). However, the question of DSS would be addressed sooner through combined analysis with two parallel trials: RAVES and GETUG-17 (see [Section 9.6](#)).

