**Table 5: Summary of timing of case report forms (CRFs)**

| TRIAL CASE REPORT FORMS                                                                       | TIMING FROM RANDOMISATION                                                       |
|-----------------------------------------------------------------------------------------------|---------------------------------------------------------------------------------|
| Baseline Information form (CRF 1a)                                                            | Pre-randomisation                                                               |
| Patient History Form (CRF1b)                                                                  | Pre- or Post-randomisation                                                      |
| Co-morbidity form (CRF 2)                                                                     | Within two weeks prior to randomisation                                         |
| PSA History Log                                                                               | Pre-randomisation                                                               |
| Randomisation forms
(CRF 3 = RADICALS-RT and RADICALS-HD )
(CRF 4 = RADICALS-HD alone ) | At randomisation                                                                |
| Radiotherapy forms (CRF 5)                                                                    | After administration of radiotherapy                                            |
| Follow-up forms*(CRF 6)                                                                       | Month 4, 8, 12, 16, 20, 24, 30, 36, 42, 48, 54, 60, then annually until year 15 |
| Patient Reported Outcome forms**                                                              | Pre-randomisation, 1, 5 and 10 years                                            |
| Disease Event form (CRF 7)                                                                    | As needed                                                                       |
| Serious adverse event form (CRF 8)                                                            | As needed                                                                       |
| Death Report form (CRF 9)                                                                     | As needed                                                                       |

\*Timed from most recent randomisation

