### 6.2.4 EARLY REPORTING OF BIOCHEMICAL OUTCOMES

In early 2018, based on the number of primary outcome events in the control arm of the RADICALS-RT comparison, the target number of events was not forecast to occur until 2025. This is several years later than originally expected due to the low event rate. Two other randomised controlled trials (RCTs), RAVES and GETUG 17, also address the question of deferred RT and are planning to report in 2018/2019. The ARTISTIC project is a pre-planned individual patient data meta-analysis, combining RAVES, GETUG-17 and RADICALS-RT. The RADICALS TMG therefore agreed, in February 2018, to publish the Freedom from biochemical progression results of RADICAL-RT to coincide with the other two trials, and enable a timely meta-analysis.

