### 6.3.2 RADICALS-RT SAMPLE SIZE

In the patients suitable for this randomisation, the control arm is assumed to be deferred radiotherapy i.e. radiotherapy at PSA relapse.

When the trial was originally designed, there was uncertainty about the likely event rate but it was anticipated that a modest absolute effect in the order of 5% would be required to convince clinicians to adopt adjuvant radiotherapy for all patients. The original sample size calculations anticipated that around 2,600 patients would need to be recruited over 5½ years and followed-up for a further 7 years in order to obtain 80% power to detect an improvement from 70% to 75% or 90% power to detect an improvement from 80% to 85%.

From SWOG 8794 and EORTC 22911, the proportion of patients free of distant metastases at 10 years is estimated to be 90%. We would look to test whether adjuvant RT can improve this to 95% (hazard ratio 0.487), which is seen as the minimum clinically significant improvement required to routinely introduce adjuvant RT to this patient population; this mirrors the size effect observed in SWOG 8794. This is tested using the superiority design. With 80% power, a two-sided 5% significance level, accrual lasting 5½ years (reaching peak accrual rates after 3 years) and a further 7 years of follow-up, we would need to recruit 1,063 patients in order to observe 66 distant metastases events. This sample size assumes that 30% of patients are lost to follow-up and around 30 patients per month randomised from 30 months onward. Therefore, the target sample size will be reduced from 2,600 to around 1,063 patients. This assumes that 30% of patients are lost to follow-up between 5 and 10 years.

If the peak accrual is lower, at around 25 patients per month, accrual would be extended by 1 year, to around 6½ years and around 1,160 patients would be randomised; this should address the question with the same power and in the same overall timescale.

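### Section 6.2.1 still projects 80% DSS power for RADICALS-RT at 18.5 years; on the later event forecast in section 6.2.4 it would be about 58–64%, and below 80% even on the 2022 date

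*Combined protocol and SAP*

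**What the plan says.** Section 6.2.1 makes DSS a secondary outcome for RADICALS-RT and gives two linked power statements. At the main metastasis analysis, "the trial would expect around 41 deaths from prostate cancer and would have 59% power" for a rise in 10-year DSS from 94% to 97%. Then "RADICALS-RT could attain 80% power for DSS after additional 6 years of follow-up (total duration of the trial would be 18.5 years"). The paragraph adds that a combined analysis with RAVES and GETUG-17 should answer the DSS question sooner.

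Section 6.3.2 sets out the design behind this: 1,063 men, 66 primary events, 5½ years of accrual plus 7 of follow-up, a two-sided 5% level, and a loss assumption ("This assumes that 30% of patients are lost to follow-up between 5 and 10 years").

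Section 6.2.4 reports a forecast made in early 2018 from control-arm events: "the target number of events was not forecast to occur until 2025". It attributes the delay of several years to the low event rate. The Trial Duration section confirms that event rates fell further after the change of primary outcome. The Duration row of the Trial Summary, in the same February 2020 version, plans assessment of RADICALS-RT and RADICALS-HD outcomes in 2022.

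**The concern.** The DSS projection carries its own clock. If 80% power comes six years after the main analysis and at 18.5 years in total, the main analysis is at 18.5 − 6 = 12.5 years, which matches 5½ + 7. Section 6.2.4 moves the primary event target to 2025, almost onto the 18.5-year date. The 59% milestone and the 80% milestone then nearly coincide, which cannot be right.

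At stake is what RADICALS-RT alone can say about prostate cancer death. Section 6.2.1 holds the only DSS power statement for this comparison under the current design. A reader who takes it at face value would assume a 20% chance of missing a halving of prostate cancer death at about 18.5 years. On the 2025 forecast that chance is about 36–42% (100% minus 58–64%).

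**Working it through.** **Inputs.** Section 6.2.1: DSS 94% against 97% at 10 years, 41 deaths, 59% power, 18.5 years. Section 6.3.2: the design values above. Trial Summary: 1:1 allocation and 1,396 men recruited to RADICALS-RT. Section 3.2: RADICALS-RT closed in June 2015. Regulatory approval is dated April 2007. The two-sided 5% level is stated for the metastasis calculation ("With 80% power, a two-sided 5% significance level, accrual lasting 5½ years") and assumed to apply to DSS.

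**1. Reproduce the stated 59%.**
- HR = ln(0.97)/ln(0.94) = 0.492.
- Freedman power = Φ(√d × (1−HR)/(1+HR) − 1.96). With d = 41: √41 × 0.3402 = 2.179, and Φ(0.219) = 58.7%. The plan says 59%.
- Schoenfeld power = Φ(√d × |ln HR|/2 − 1.96) = 62.1% at 41 deaths.
- Freedman events for 90% against 95% (HR 0.487) come to 66, as stated; Schoenfeld gives 61. Freedman therefore matches the plan's figures.

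**2. Deaths needed for 80% power.**
- Freedman: (1.960 + 0.842)² / 0.3402² = 67.8, so 68.
- Schoenfeld: 4 × (1.960 + 0.842)² / 0.7087² = 62.5, so 63.

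**3. Was 80% reasonable in 2011?** The model has 1,063 men, 5.5-year accrual with a linear ramp over 3 years, and exponential hazards.

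| Loss to follow-up | Deaths at 12.5 y | Deaths at 18.5 y | Power at 18.5 y, Freedman / Schoenfeld |
|---|---|---|---|
| 30% in years 5–10 | about 41 | about 60–61 | about 76% / 79% |
| None | 43.5 | 71 | 82% / 85% |

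The stated 80% lies between these rows, so it was roughly right on its own inputs.

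**4. Apply the current forecast.** The model has 1,396 men, accrual to June 2015, and hazards scaled so that 66 primary events fall at the forecast date. Deaths are anchored at 41 at that date. The start is varied from April 2007 to early 2008, and loss is none or 30% in years 5–10.

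| Target reached | Trial year | Deaths at 18.5 y | Freedman | Schoenfeld |
|---|---|---|---|---|
| During 2025 | about 17–18.7 | 40–47 | 58–64% | 62–68% |
| Mid-2022 | about 14.3–15.2 | 51–58 | 68–74% | 71–77% |

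Letting the target fall anywhere within 2022 widens the second row to about 66–76% (Freedman) or 70–79% (Schoenfeld), still below 80%. Without the 41-death anchor the model gives about 39 deaths at the milestone, which lowers power slightly.

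**5. A check that does not use the 41-death anchor.** Every prostate cancer death is itself a primary event (section 5.2.2). With 66 primary events in 2025, the same model gives about 65–75 by year 18.5. Reaching even 63 deaths would need 63/75 = 84% to 63/65 = 97% of men with a primary event to have died of prostate cancer. The plan's own ratio is 41/66 = 62%, and section 6.2.1 says that time from metastasis to prostate cancer death has lengthened.

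**The case against.** The strongest objection is that the size depends on choices the documents do not settle. The 2025 date is a 2018 forecast from control-arm events, and how it maps to 66 events over both arms is not shown. No current prostate cancer death count is given, the 41:66 ratio may have changed, and the Trial Summary gives 2022. This stands against any single figure. A reader might infer that power at 18.5 years is simply about 59–65%; the documents support that only conditionally on 2025. If 2022 means analysing before 66 events, the link to 41 deaths fails altogether, and deaths at that analysis would be fewer.

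A reader might also infer that 80% was too optimistic from the start. The documents do not support this. The design inputs give about 76–79% with the stated loss and 82–85% with none, and the plan's loss settings for DSS are not shown. National death registration (section 5.7.1) could make loss matter less for deaths. Adding other-cause mortality of 18% at 10 years, inferred from section 6.2.1's one-in-four share, gives 37.7 deaths at 12.5 years. That does not reproduce the stated 41, so it is not the plan's model.

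Finally, the sentence is hedged, DSS is secondary, no DSS analysis is scheduled at 18.5 years, and the combined analysis is expected sooner. All true. This limits the consequence but does not make the sentence current.

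**Conclusion.** The point holds as a failure to update. On the protocol's own 2025 forecast, DSS power at 18.5 years is about 58–64% (Freedman) or 62–68% (Schoenfeld), against 80% stated. With the target reached in mid-2022 it is about 68–74% or 71–77%. The 63–68 deaths needed are not reached in either case.

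This rests on a trial clock starting between April 2007 and early 2008, an event target of 66, about 41 prostate cancer deaths when it is met, exponential hazards, and a two-sided 5% level. The exact power is uncertain; the shortfall from 80% persists across the ranges tried. It affects the stated power of a secondary outcome, not the primary analysis.

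**What to change.** In section 6.2.1, delete the 80%-at-18.5-years sentence or restate it as a projection made on the 2011 assumptions. State that DSS power is about 59% at about 41 prostate cancer deaths and that 80% needs about 63–68. Re-project the date for that number from current pooled death counts, not counts by arm. Reconcile the 2025 forecast in section 6.2.4 with the 2022 assessment date in the Trial Summary before writing either date into the DSS paragraph. Keep the existing pointer to the combined analysis with RAVES and GETUG-17.

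The cost is a wording change and one recalculation, with no new patients, data collection or comparative unblinding. The downside is a less favourable stated power for a secondary outcome.

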#### 6.2.2 PRIMARY OUTCOME MEASURE – RADICALS-HD

After 2011, when the primary outcome in RADICALS-RT was amended to freedom-from-distant-metastasis, the primary outcome measure in RADICALS-HD was unchanged and remained disease-specific survival (DSS). Causes of death in patients diagnosed with prostate cancer can be difficult to confirm. A reported death from prostate cancer would be expected to be preceded by a report of hormone refractory metastatic prostate cancer. The clinician's discretion should be used to decide if death during treatment is related to prostate cancer. All UK patients will be flagged with the NHS

Central Register (NHSCR) or equivalent for mortality data to support the data collected on the case report forms (CRFs).

Measures such as central flagging ensure that deaths are captured on the database in an accurate and timely manner. However, the number of deaths from prostate cancer in RADICALS-HD patients continued to be very low and it became apparent that neither the 0 vs 6 month or 6 vs 24 month comparisons would accrue sufficient events for analysis within a realistic timeframe. Deaths from other causes also presented a problem for analysis as a competing risk, even though numbers of 'all cause' deaths were also lower than expected. It was therefore decided that the primary outcome of RADICALS-HD would now be metastases-free survival (**MFS**).

